#### 2.4.1. Quality of Life

The KidsLife Scale, a questionnaire specifically designed for Spanish individuals with ID, will be used to assess the impact of both programs on participants’ QoL. This scale consists of 96 items organized into eight QoL domains and must be completed by a family member or caregiver. When administered to a sample of young 121 individuals with ID, the scale demonstrated good internal consistency, with Cronbach’s alpha values ranging from 0.812 to 0.949. Additionally, construct validity evidence provided by Confirmatory Factor Analysis indicated adequate fit indices [30].

#### 2.4.2. Functionality

Dynamic Balance and Gait Speed: The “Timed Up and Go Test” (TUGT) will be employed, a reliable assessment tool for individuals with ID [31]. In a sample of 31 adults with ID, the TUG proved to be a feasible assessment tool, demonstrating excellent test–retest reliability (ICC: 0.90; 95% CI: 0.82–0.95) [32];Flexibility: The sit and reach test (SR) will be used to assess the impact of the program on the participants’ lower-body flexibility. For performing the SR, the participants will sit on the floor without shoes and with knees straight, and feet placed flat against the front-end panel of a standard SR box. Then, they will be asked to slowly reach forward as far as possible while placing the palms down along the measuring scale placed on the top of the box and to hold the position for approximately 2 s. The most distant point reached with the fingertips will be recorded (to the nearest centimeter). The best of two trials will be retained for analysis. The SR has demonstrated high reliability in a sample of 63 adolescents with ID (ICC = 0.97) [33] and has been previously used to assess fitness levels in adults with ID [34];Cardiorespiratory Fitness: Heart rate (HR) data will be collected using a Polar HR monitor (Polar Team Pro for iPad, version 1.0.1) during the tests. This method has been previously applied to individuals with ID [3].

#### 2.4.3. Feasibility of the Programs

The following variables would be recorded by the people who will administer the exercise programs to assess their feasibility: recruitment rate (number of participants recruited from those that fulfilled the inclusion criteria) [35]; attrition (number of drop-outs); completion rate (number of participants who completed each outcome measure); adherence measurement with comprehensive reporting [36] (proportion of participants with participation rates exceeding 80%); participation (total of exercise hours completed divided by the total number of possible hours); and safety and tolerability (number of participants who experienced exercise-related adverse effects, such as pain, dizziness, intense fatigue, falls, etc., resulting from exercise performance). Participants may experience some discomfort, fatigue, or muscle soreness, which are common among sedentary individuals starting a physical activity intervention. However, these effects typically diminish after two or three sessions [37].

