Regarding the Fit 5-Fitness Cards, the limited existing research has demonstrated their effectiveness in improving body composition and metabolic health among Special Olympic athletes [19]. However, only one study appears to have been conducted specifically with individuals with ID. In the study by Ptomey et al. [26], the Fit 5-Fitness Cards were utilized to promote physical activity among adults with ID as part of a comprehensive weight management intervention. This highlights the clear need for further research to evaluate the efficacy of this strategy in individuals with ID.

Therefore, the primary objective of this study is to evaluate the effect of the NW program on the QoL and functionality of individuals with ID. Additionally, the secondary objectives include assessing the impact of the Fit 5-Fitness Cards program on QoL and functionality, as well as comparing the safety, feasibility, and adherence of these two alternative exercise interventions.

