### 2.5. Intervention

Before the intervention allocation is revealed, the monitors/caregivers will receive training on both interventions to ensure that the explanations and implementation are as consistent as possible across all centers.

Both exercise training programs would be performed at the rate of two 60 min sessions per week for three months. After the wash-out period (one month), the training programs will be performed in reverse order for another three months. A follow-up phase of six months is scheduled once the intervention has finished (7 months).

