### 2.6. Statistical Analysis

Data will be reported as medians and interquartile ranges for non-normally distributed variables (checked with the Kolmogorov-Smirnoff test) or as means and standard deviations for normally distributed variables. Qualitative variables will be reported as n (%). The intra-cluster correlation coefficient and the cluster-specific effects will also be calculated. Inter-group quantitative variables will be compared, including the primary outcome, with an unpaired, two-tailed t test or the Mann–Whitney U test, as applicable. For inter-group dichotomous data comparison, the two-tailed chi-square tests will be used, with the Yates correction or Fisher’s exact test as appropriate. For repeated measures analysis, the two-way analysis of variance with the Bonferroni correction or the Friedman test, as appropriate, will be used. Comparison will be adjusted by cluster effect. Subgroup analysis of the primary outcome will include sex, age, BMI (normal, overweight and obese), level of physical activity (Inactive, Active), and level of ID (mild, moderate, severe). Multivariate regression models will adjust for confounders such as sex, age, BMI, physical activity, and ID level. Multicollinearity will be checked using the Variance Inflation Factor (VIF), with VIF > 5 indicating high collinearity [42]. Sensitivity analyses will assess robustness. Statistical significance will be set at a two-tailed *p*-value of less than 0.05. All analyses will be conducted using SPSS v24.0 software (IBM Corp., Armonk, NY, USA).

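### Safety is a count of participants with any exercise-related effect, with falls not separated and no exposure denominator, so unequal attendance or common minor complaints could distort the programme comparison

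*Protocol article*

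**What the plan says.** Section 2.4.3 (Feasibility of the Programs) defines safety and tolerability as the "number of participants who experienced exercise-related adverse effects, such as pain, dizziness, intense fatigue, falls, etc., resulting from exercise performance". The unit is the participant, not the event. The definition gives no severity grade, breakdown by type, exposure denominator or observation window.

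The same paragraph goes on to say: "Participants may experience some discomfort, fatigue, or muscle soreness, which are common among sedentary individuals starting a physical activity intervention". It adds that "these effects typically diminish after two or three sessions". It does not say whether such effects enter the safety count.

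Exposure is recorded in that paragraph as a separate variable, participation, defined as the "total of exercise hours completed divided by the total number of possible hours". It is not linked to the safety count.

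The Introduction lists among the secondary objectives "comparing the safety, feasibility, and adherence of these two alternative exercise interventions", and the Discussion repeats this. Section 2.5 plans "two 60 min sessions per week for three months" for each programme. For yes/no outcomes, section 2.6 says: "For inter-group dichotomous data comparison, the two-tailed chi-square tests will be used", with a continuity correction or Fisher's test as needed. It also says comparisons will be adjusted for cluster. No exposure term is named.

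**The concern.** A count of people with at least one event rises with the number of sessions attended. If one programme is attended less, fewer of its participants will be flagged even when each session carries the same risk. Adherence is itself an outcome to be compared, so equal attendance cannot be taken for granted.

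Separately, a single list gives a participant with pain or dizziness the same weight as one who fell. If minor complaints are common under both programmes, they fill most of the count and a difference in falls barely shows.

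At stake is the safety comparison that the article sets as an objective. A tally of affected participants also cannot be split afterwards into falls and other complaints, or turned into event rates. The recording therefore has to be settled before data collection.

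**Working it through.** The article gives no adverse-event rate, safety margin or attendance figure, so there is no stated result to reproduce. The rates below are assumptions chosen to show direction and size.

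**Inputs**
- Planned sessions per programme: 2 per week over three months (section 2.5). Thirteen weeks give 2 × 13 = 26 sessions; twelve weeks would give 24.
- Attendance *a*: assumed 90% in one programme and 60% in the other, so 23.4 v 15.6 sessions out of 26.
- Risk of any event per attended session *p*: assumed from 0.005 to 0.10, sessions independent.

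**1. Attendance, equal constant risk.** P(at least one event) = 1 − (1 − *p*)^(26*a*). For *p* = 0.02: 1 − 0.98^23.4 = 37.7% and 1 − 0.98^15.6 = 27.0%.

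| *p* per session | 90% attended | 60% attended | Ratio |
|---|---|---|---|
| 0.005 | 11.1% | 7.5% | 0.68 |
| 0.01 | 21.0% | 14.5% | 0.69 |
| 0.02 | 37.7% | 27.0% | 0.72 |
| 0.05 | 69.9% | 55.1% | 0.79 |
| 0.10 | 91.5% | 80.7% | 0.88 |

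The less attended programme shows 12% to 32% fewer affected participants, although the rate per session is identical by construction. Using 24 sessions changes little: at *p* = 0.02 the figures are 35.4% v 25.2%.

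**2. The order can reverse.** Take risk 0.020 at 90% attendance and a 30% higher risk, 0.026, at 60%. Then 1 − 0.98^23.4 = 37.7% and 1 − 0.974^15.6 = 33.7%. The programme with the higher risk per session shows the lower count.

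**3. Early clustering of events.** Section 2.4.3 expects complaints mainly in the first two or three sessions. Assume risk 0.20 in sessions 1–3 and 0.01 afterwards.
- If absence comes late: 1 − 0.80³ × 0.99^(26*a* − 3) gives 58.3% v 54.9%, so the gap nearly closes.
- If sessions are missed at random: 1 − (1 − 0.20*a*)³ × (1 − 0.01*a*)^23 gives 55.2% v 40.7%, so the gap remains.

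**4. Dilution of falls.** This needs no attendance difference. With soreness in a share *s* under both programmes, counted as an event, and falls in a share *f*, independent of each other, the count is 1 − (1 − *s*)(1 − *f*). For *s* = 0.40 and *f* = 0.10 v 0.03: 1 − 0.60 × 0.90 = 46.0% and 1 − 0.60 × 0.97 = 41.8%. A ratio of 3.33 for falls becomes 1.10 for the count. At *s* = 0.30 it is 1.15, and at *s* = 0.50 it is 1.07.

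**The case against.** The strongest reply is that this is a condensed article about a self-described pilot, and that the number of participants with at least one related event is a conventional summary. Grading, listings by type and exposure-adjusted rates may sit in a full protocol or analysis plan that is not shown, and the list of effects is introduced as examples. Participation hours and drop-outs are reported alongside, so unequal exposure would be visible. Each participant is also scheduled for both programmes.

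Part of this stands. The count is a legitimate supplementary line, and what an article omits is not an error. But here the article states a definition, and that definition feeds a stated comparison. Visible attendance figures do not convert a participant count into rates or isolate falls, and the crossover does not make attendance equal between programmes.

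Four stronger readings are tempting, and the article does not support them:
- *The trial expects attendance to differ between programmes.* No section says so. The Discussion anticipates that both programmes will be enjoyable, and the only decline in adherence it foresees is in the unsupervised follow-up.
- *The less attended programme will look safer.* That needs a real attendance gap without an offsetting difference in risk. A programme with enough extra risk would still look worse, and poor tolerability may itself lower attendance.
- *Early soreness counts the same as a fall.* Pain and intense fatigue are listed as adverse effects, while discomfort and soreness are described separately as expected. The text can be read either way.
- *Each count covers a whole programme.* This is a reasonable inference from the measurement schedule in section 2.4.5, but no window is stated.

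The attendance and early-soreness arguments also partly offset each other, as step 3 of the working shows. They cannot both apply at full strength.

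**Conclusion.** The point holds in a conditional form. As defined, the safety measure does not separate falls from lesser complaints and takes no account of exposure, although it serves a between-programme comparison.

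If attendance were 90% v 60%, equal risk per session would appear as 12% to 32% fewer affected participants in the less attended programme. The gap is smaller where events cluster early and absence comes late. If minor complaints affected 40% under both programmes, falls in 10% v 3% would appear as 46.0% v 41.8%. These sizes rest entirely on assumed rates, independent sessions and, for the second, soreness being counted. Whether it is counted is itself unclear and should be stated.

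This is a cheap improvement to recording and reporting. It does not show that the planned comparison will mislead.

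**What to change.** In section 2.4.3:
1. Log each event by type, at each session, on the attendance record.
2. For each programme, report falls separately and other events by type, per 100 sessions (or hours) attended.
3. State whether expected discomfort and soreness in the first two or three sessions are counted, and show them separately from later events.
4. Keep the number of participants with any event as a supplementary line.

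The staff who run the programmes already record exercise hours completed, so no new exposure data are needed. The cost is slightly more recording per session. Nothing in the interventions changes.

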### 2.3. Procedures

The registered sites will be randomly assigned to two groups using a random number table generated in Excel. The randomization process will be unrestricted, with no stratification or pairing of sites. To minimize selection bias, allocation concealment will be ensured by having an independent researcher generate the randomization sequence and store it in a secure file. Following the recruitment of the participating sites and the completion of the training period for monitors/caregivers, the randomization table will be unblinded, and the sites will be allocated to one of two groups. Preferably, the monitors/caregivers will be occupational therapists, physiotherapists, or social workers with specialized training in adapted exercise.

Group A will initially implement the NW program, followed by the Fit 5-Fitness Cards program. Conversely, Group B will undertake the programs in the reverse order. The random sequence will be generated by [name], while [name] will be responsible for informing the registered sites of the exercise sequence their members are required to follow.

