### 2.4. Measurements

To assess the effects of the training programs, functionality tests will be selected based on the following criteria: (a) proven feasibility for individuals with ID; (b) ease of execution with limited resources; and (c) the ability to perform the tests within the registered facilities.

Participants will receive a detailed explanation of the protocols, be allowed to practice the tests in advance, and receive guidance throughout the assessment process. Neither the monitors nor the participants will be blinded to the interventions.

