#### 2.5.2. Fit 5-Fitness Cards

The Fit 5-Fitness Cards program is a structured approach focusing on four key areas of physical fitness: endurance, strength, flexibility, and balance. The sessions include simple exercises tailored to different skill levels, organized into progressive stages (levels 1 to 5) to match the abilities of each participant [18]. Participants will engage in 60 min sessions conducted on non-consecutive days over the course of three months.

The sessions will be led by a graduate in Sport Science with over six years of experience training special populations. Additionally, an instructional video will be provided to support users in performing the exercises during each session. This will ensure consistency across the different centers.

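### The safety outcome counts only effects deemed exercise-related, and the only recorders named are unblinded delivery staff, so uneven attribution could distort the safety comparison

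*Protocol article*

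**What the plan says.** Section 2.4.3 lists six feasibility indicators. The last, safety and tolerability, is the "number of participants who experienced exercise-related adverse effects, such as pain, dizziness, intense fatigue, falls, etc., resulting from exercise performance". The section says who collects all six: "The following variables would be recorded by the people who will administer the exercise programs to assess their feasibility". Section 2.4 states: "Neither the monitors nor the participants will be blinded to the interventions".

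Safety is also meant to be compared. The Introduction gives as a secondary objective "comparing the safety, feasibility, and adherence of these two alternative exercise interventions", and the Discussion repeats it. Section 2.6 supplies the test for yes/no outcomes: "For inter-group dichotomous data comparison, the two-tailed chi-square tests will be used", with a continuity-corrected or exact alternative.

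Two further statements bear on how the judgement might be made. Section 2.4.3 treats some effects as ordinary: "Participants may experience some discomfort, fatigue, or muscle soreness, which are common among sedentary individuals starting a physical activity intervention". On staffing, section 2.3 says that, preferably, "the monitors/caregivers will be occupational therapists, physiotherapists, or social workers with specialized training in adapted exercise", whereas section 2.5.2 says of Fit 5: "The sessions will be led by a graduate in Sport Science with over six years of experience training special populations".

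**The concern.** The definition requires a causal link to exercise twice over, so a participant is counted only after someone has decided that the effect came from the exercise. Relatedness thus becomes a condition for entering the outcome, when it could be a property recorded about an event.

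That matters because the outcome is to be compared between two different activities. A stumble on a path with poles and a sore shoulder after a strength card may not invite the same causal judgement. If relatedness is judged more readily in one programme, the counts differ with no difference in harm. If real effects of one programme are more often put down to other causes, a true excess shrinks. A comparison restricted to related events cannot by itself tell these situations apart.

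**Working it through.** The document states no adverse event rate, safety margin or safety power, so there is no figure to reproduce. The check has a textual part and an illustration on assumed values.

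**Text.** Set side by side:
- Sections 2.4.3 and 2.4 give an outcome filtered by relatedness, recorded by unblinded delivery staff. No other assessor is named.
- The Introduction and Discussion make the comparison of safety an objective.
- Reasons why attribution could differ by programme: section 2.5.2 names a session leader for Fit 5 whose background differs from the monitors preferred in section 2.3. Section 2.4.3 also calls discomfort and fatigue common while listing pain and intense fatigue as countable, with no stated dividing line.
- Reasons why it might not differ: every centre delivers both programmes to the same participants (sections 2.1 and 2.3), and monitors are trained in both for consistency (section 2.5).

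**Illustration, step 1: one event per affected participant.** Let p be the true risk of any event, equal in both programmes (assumed 20%), and a the probability that an event is attributed to exercise. Recorded risk = p × a, so the recorded risk ratio is (p × a₁)/(p × a₀) = a₁/a₀.
- 90% against 80%: 0.18/0.16 = 1.13
- 90% against 70%: 0.18/0.14 = 1.29
- 90% against 60%: 0.18/0.12 = 1.50
- Equal attribution: ratio 1, no distortion

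**Step 2: several events per affected participant.** The outcome counts participants, not events. If a person has k events and each is attributed independently, that person is counted with probability 1 − (1 − a)^k. For 90% against 60%:
- k = 2: (1 − 0.1²)/(1 − 0.4²) = 0.99/0.84 = 1.18
- k = 3: (1 − 0.1³)/(1 − 0.4³) = 0.999/0.936 = 1.07

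If all of a person's events are judged the same way, the counting probability returns to a and the step 1 ratios apply whatever k is. So for 90% against 60% the distortion runs from about 1.07 (three independent events) to 1.50 (one event, or fully correlated judgements).

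**Step 3: effect on a test.** With one event per affected participant, attribution of 90% against 70% and a true risk of 20% to 40%, the recorded risks differ by 0.2 × 0.20 = 0.04 to 0.4 × 0.20 = 0.08. By normal approximation, at two-sided 5% and ignoring clustering, a comparison of 50 against 50 would declare a false difference about 8% to 13% of the time. A paired comparison of all 100 participants with independent periods would do so about 12% to 22% of the time. Several independently attributed events per person would lower these figures.

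**The case against.** The strongest reply is that much of the worry concerns things the article does not say. Section 2.4.3 fixes what is counted and who records it. It does not say who judges relatedness, that unrelated events go unrecorded, or that effects arising at home are missed. Event forms and causality criteria commonly sit in a full protocol, which is not shown. A reader might infer that delivery staff make the causal judgement and that unrelated events are lost beyond recovery. The first is a reasonable inference because no one else is named, but neither is stated, and the point does not rest on them. It rests on the outcome definition, which is explicit.

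Second, bias needs attribution to differ by programme. A centre with a stable habit of over- or under-attributing applies it to both programmes, and the listed effects give recorders some common anchors. This stands as a limit. It does not remove differences tied to the activity itself, and the section 2.5 training is described as serving consistent explanation and delivery.

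Third, this is one indicator in a self-described pilot, with no stated safety hypothesis, and exercise-related effects are a coherent tolerability measure. That is fair, and it is why the related-event count should be kept. It does not justify making that count the only basis for a declared comparison.

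Fourth, counting all events leaves unblinded staff asking and recording, and adds background events that pull a true ratio towards 1. Both are correct, so neither count should stand alone. Unblinded delivery is hard to avoid in an exercise trial and is not the fault raised here.

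**Conclusion.** The point holds as a weakness in a stated outcome definition that should be changed. It is neither a contradiction nor an error of fact. A relatedness filter, with unblinded delivery staff as the only named recorders, leaves the planned safety comparison open to uneven attribution.

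A reader might go further and conclude that the comparison will be biased, or that a recorded difference would merely reflect attribution habits. The documents do not support that: no passage shows attribution differing between the programmes, and the crossover with common training works against it.

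The spurious ratios of 1.13 to 1.50 assume equal true risk, attribution gaps of 10 to 30 percentage points, and either one event per affected participant or uniform judgement within a person. With two or three independently attributed events, even the widest gap gives only about 1.18 or 1.07. None of these inputs comes from the documents.

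**What to change.** Amend section 2.4.3 as follows:
- Record adverse events during each three-month programme whatever their judged cause, including pain, dizziness, intense fatigue and falls, with the date and the programme under way.
- Use the same short fixed prompt at sessions in both programmes, put to the participant and to the caregiver where present.
- Hold judged relatedness as a separate field.
- For each programme, report side by side the number of participants with any event and the number with a related event.

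The change needs no extra staff or visits, because the prompt is used at sessions already planned. The recording load is not nil: 100 participants × 2 sessions a week × 13 weeks × 2 programmes is 5,200 short prompts, assuming 13 weeks per programme, full attendance and a prompt to each participant at every session. All-event counts will include background events that dilute a true difference, which is why the related count stays beside them. Unblinded reporting is not removed.
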